### Biospecimen and data collection methods

Each site will have a separate dedicated team of research physicians, study nurses, clinical & laboratory technicians and field workers. These site teams along with site and project managers will form a cumulative clinical research unit (CRU), who would be responsible for implementing all study-related procedures at the three sites.

Sample and data collection at the study sites, during home visits, or by telephone interviews will be conducted by the study nurses using electronic forms under the supervision of medically qualified and trained research physicians. The field workers are responsible for ensuring that participants adhere to the study follow-up schedule. A separate trained research team ensures compliance to follow-up schedules. Local research laboratory teams will collect all biospecimens, pre-processing will be carried out at each of the three study sites respectively and transported to THSTI for long term archival at the ISO20387 accredited biorepository facility following standard operating protocols to ensure sample integrity and quality.

After confirmation of eligibility and recruitment, women will undergo assessments at three time points during pregnancy corresponding with the three trimesters summarised in
Table 1 and
Table 2 respectively.

**Table 1. T1:** List of procedures and assessments at three time points during pregnancy corresponding with the three trimesters for the study participants.

	Start				Close out	
		N=600	N=600	N=600	N=600	N=100
Timepoint	t _-1_	t _0_ 11–14 weeks	t _1_ 18–22 weeks	t _2_ 30–34 weeks	t _4_ birth	t _5_ 0–16 days PN
**RECRUITMENT**						
Eligibility screen	X					
Informed consent	X					
Gestational age confirmation by ultrasound	X					
Confirmation of viable singleton pregnancy	X					
**ASSESSMENTS**						
Clinical history		X	X	X	X	
Food frequency questionnaire		X	X	X		
Heat exposure and indoor pollution measurements		X	X	X		X
Modified HOTHAPS questionnaire		X	X	X		
Urine specific gravity		X	X	X		
Maternal Haemodynamic assessment		X	X	X		
Fetal Ultrasound		X	X	X		
CTG				X		
Maternal blood sample		X	X	X		
Birth and newborn outcomes					X	
Lactation study (100 women only in GCH)					X	X

**Table 2. T2:** List of planned clinical samples with their processing methods and planned future course of analysis.

The sample collection, processing methods are summarized in Table 4: Biospecimen	Time of collection	Method of collection	Immediate processing at study site	Transportation time to storage at biorepository	Long term storage	Studies*
Maternal Blood -5 ml (EDTA tube)	11–14 weeks 18–22 weeks 30–34 weeks Time of Delivery	Venepuncture	1. Stored as buffy coat 2. Processed to plasma	In liquid nitrogen (-196 ° C) / within 8 hours for GCH site and in Dry Ice for other two sites	Deep freezers (-75 °C)	Biobanking, biochemistry,
Maternal Blood (plain tube) – 5 ml	11–14 weeks 18–22 weeks 30–34 weeks Time of Delivery 15 days post delivery (pre and post feed)	Venepuncture	Processed to sera	In liquid nitrogen (-196 ° C) / within 8 hours for GCH site and in Dry Ice for other. two study sites	Deep freezers (-75 °C)	Biobanking, biochemistry,
Breast milk	First and 15 days post delivery	Manual expression	Stored in 0.5 ml aliquots up to a total volume of 5 ml	In liquid nitrogen (-196 ° C) / within 8 hours for GCH site and in Dry Ice for other. two study sites	Deep freezers (-75 °C)	Biobanking, biochemistry

### Measurement of potential confounders

To adjust for potential confounding factors, comprehensive baseline information will be collected from all participants at enrolment and updated at each subsequent visit. This includes socio-demographic details (e.g., maternal age, education, occupation, household income, type of housing material, and access to cooling resources), medical and obstetric history (e.g., parity, prior adverse pregnancy outcomes, chronic health conditions), and social factors (e.g., marital status, family support, and migration status). Dietary intake will be assessed using site-specific Food Frequency Questionnaires (FFQs), adapted and validated for the local population where possible along with physical activity using the International Physical Activity Questionnaire (IPAC)
^
8
^. These FFQs will capture habitual intake of major food groups and specific nutrients relevant to pregnancy and heat vulnerability. Housing structure and ventilation characteristics, source of water and sanitation, and presence of cooling appliances (e.g., fans, air conditioners) will also be recorded through structured interviews and home visit observations. These variables will be used in subsequent analyses to adjust for confounding and assess effect modification in the relationship between environmental exposures and maternal or neonatal outcomes.

Within the overall design of the study, expert work groups have been convened to design and oversee the capture of key exposure and outcomes, which are given below. This protocol will outline the aims of each component and methods for sample/data capture.

### Individual environmental exposures

Heat events in this study are defined using three approaches: (1) the India Meteorological Department (IMD) definition of a heatwave; (2) threshold exceedance of wet bulb globe temperature (WBGT) values based on international occupational safety guidelines
^
9
^; and (3) statistical exceedances, including continuous measures and the 95
^th^ percentile of local temperature distributions. This multi-pronged definition allows us to capture both acute and chronic heat stress relevant to maternal and foetal outcomes. The full list of terms is given as a glossary at the end of the manuscript.

To determine ambient heat exposure, satellite-based temperature via global positioning system (GPS) coordinates and humidity data, with microenvironmental measurements, will be integrated. For home-based assessments, data will be captured over 24 hours once per trimester using ground-based instruments (EL-USB-2-LCD+ data logger, and iButton Hygrochron) and 4–5 heat exposure measurements using Questemp°34 3M WBGT Monitor. A sub-study with repeated assessments (48–72 hours) will be conducted in ~10% of participants at each site. This will allow estimation of within-and between-day variance, supporting regression calibration or other error-modelling approaches. Additionally, if the woman is working, workplace exposure will be captured during an 8-hour shift (pre-shift, multiple during the shift, and post-shift) each trimester, American Conference of Governmental Industrial Hygienists (ACGIH) screening limits (i.e., preliminary heat exposure thresholds used to identify potential health-related health risks in the workplace) and a professional Industrial Hygienist’s judgement will determine the pregnant woman’s workload category (Heavy or moderate job type). The Threshold Limit Value (TLV) will be calculated by obtaining spot readings during the work shift/working time and by workers/participants describing workload, using a "clo" factor of 0.6 for summer work uniforms. This "clo" component contributes to a WBGT correction factor. Since no such standards exist for the general population, the same ACGIH standards will be applied to the general population as the study participants include both working mothers and non-working mothers who perform moderate to heavy-intensity household activities such as cooking, cleaning, and childcare, making the activity relevant to occupational standards appropriate for our context.

These measurements will be spatially and temporally linked to satellite-derived meteorological data via GPS and timestamps, allowing for triangulation of heat exposure levels, adjustment for spatial variability, and improved resolution. The satellite-based temperature and humidity data retrieved for the entire pregnancy will be incorporated to complement individual-level measurements, supporting a more comprehensive assessment of cumulative heat exposure. By combining home and workplace measurements, this approach holistically captures heat exposure and its health impacts, ensuring a complete assessment of each woman’s complete environmental burden.

Personal heat exposure measurements will be captured using EasyLog USB temperature and humidity data loggers and wearable devices validated against the gold-standard Quest Temp°34 3M WBGT Monitor to calculate the WBGT heat index. The EasyLog USB data loggers will be deployed in a fixed location in the participant’s home for 24 hours to capture continuous area-level data. These devices are not worn; instead, they remain stationed in a participant’s key microenvironment throughout the monitoring period and are retrieved after for data download. Wearable devices in this study include the Fitbit Sense 2 smartwatch and iButton sensors. The Fitbit tracks maternal heart rate while the iButtons, one mounted below and another above the strap, measure the skin temperature and personal microclimate or ambient temperature, respectively. The iButtons are validated tools for capturing ambient temperature exposure in field settings and have been widely used in heat stress research
^
10
^. They measure temperature at 5-second intervals for 24 hours to assess individual thermal exposure and provide a low-burden, non-invasive method for continuous monitoring. Combined, these wearables provide a detailed profile of the interaction between environmental conditions and maternal physiology during daily routines. Area heat exposure will also be recorded with the Quest Temp°34 monitor. The WBGT Heat Index was selected over other indices due to its practicality and wide usage in occupational and environmental health studies. WBGT is an internationally recognised index for assessing occupational heat stress and aligns with ISO standards, particularly in settings where radiant heat and humidity are significant. The exposure data obtained will be used for the calculation of the WBGT heat index using the standard formula (ACGIH 2021). The Quest Temp°34 3M WBGT Monitor will serve as the field reference instrument. All devices will undergo pre-deployment bench checks across expected temperature and humidity ranges. The EasyLog data logger and iButton devices will be co-located with QuestTemp WBGT for ≥ 24 hours to characterise bias and precision. A rotating panel of devices will be deployed across sites quarterly to detect drift or site-specific bias. Correction equations (linear or GAM) will be derived from co-location data. Devices will be flagged for recalibration if bias means exceed 0.5°C or limits of agreement exceed ± 1.5°C; data failing QC will be excluded or imputed using measurement-error-aware methods.

Physiological heat strain will be captured via urine specific gravity measures, temperature, heart rate, and blood pressure measurements. Urinary specific gravity will be measured during a home visit in each trimester using the ATC (REC-200 ATC) clinical handheld refractometer and Dirui H10 urine dipstick. Blood pressure will be measured with the participant seated comfortably, from the brachial artery measured at the level of the heart, using an Omron HEM 7120 sphygmomanometer once per home visit and pre-shift and post-shift in working pregnant women. Core body temperature via tympanic membrane will be measured using a Rossmax RA600 infrared thermometer once per visit. Heart rate will be measured using Fitbit Sense 2 watches.

Area level heat metrics, from WBGT and Easy Log USBs, and personal exposure data from iButtons are synchronised with physiological parameters such as heart rate, core body temperature, and Urine Specific Gravity. This enables a composite understanding of external heat stress and internal physiological heat strain. All devices are time-synchronised upon starting and periodic calibration and QC procedures described above will be implemented to maintain data quality, and finally data are analysed jointly to determine how environmental conditions translate into physiological responses during pregnancy.

Quantitative data on women's perceptions of heat stress impacts, hydration, and productivity will be gathered using a modified High Occupational Temperature Health and Productivity Suppression (HOTHAPS) questionnaire. The original HOTHAPS tool was developed for occupational settings to assess heat stress impacts on health and work capacity. This version includes pregnancy-specific items and contextual modifications relevant to Indian conditions, such as household labour, rest patterns, clothing, and heat-adaptive behaviours
^
6
^.

To capture air pollution also exposure, indoor PM 2.5 measurements will be taken along with the heat stress parameters using an indoor monitor (Aurassure Care Real Time Personal Air Particulate Matter Monitor), calibrated to the local pollution monitoring station corresponding to the three clinical sites for a continuous period of 1 week to account for daily variations.

Quality Control (QC) monitoring for environmental exposure assessment will be done contemporaneously throughout the study using a decentralised data transfer pipeline to facilitate the cleanup and verification of the exposure assessment data collected from all three sites. This digital platform will help to limit travel needed for the exposure assessment team (based in Chennai) and will thus help to reduce our study-associated carbon footprint.

### Maternal haemodynamic assessment

It is hypothesised that the effects of heat exposure on the maternal circulation may depend on the gestational age at exposure. Specifically: (i) early pregnancy maternal hemodynamic disruptions will directly impact early placental development and increase the risk of preeclampsia and other hypertensive disorders of pregnancy, whilst (ii) mid-to-late pregnancy hemodynamic changes may influence cardiovascular load, leading to maternal cardiovascular maladaptation, which could lead to changes in the uteroplacental circulation.

Maternal hemodynamic status, including pulse, blood pressure, Cardiac output (CO), and total peripheral vascular resistance (TPVR), will be measured each trimester using the USCOM 1A® pulsed wave monitor. The USCOM 1 A is a non-invasive, portable machine that utilises continuous wave Doppler technology and it has been validated for use in pregnancy
^
11
^. 

All examinations will be undertaken under standardised conditions using the same equipment in each site. Women will be asked to sit quietly for 5 minutes before the commencement of the investigations. A brachial blood pressure reading will be recorded using the appropriate cuff size from the right arm of the participant. Participant height (cm) will be measured during enrolment, and weight (kg) will be recorded at the time of each assessment. Two USCOM readings will be taken at an interval of 1 minute apart, with the average of the two readings used for analysis. Participants with abnormal hemodynamic results will be referred to a hospital physician for appropriate care, facilitated by the study staff.

### Fetal and placental ultrasound and CTG assessments

It is also hypothesised that ambient heat exposure could alter Uterine Artery (UtA) flow, which in the first trimester could lead to poor trophoblast invasion, and increased risk of preeclampsia and other placental disorders
^
12
^, whilst later in pregnancy could alter umbilical artery Doppler readings. This reduction in perfusion could lead to lower fetal oxygen levels, causing blood redistribution to vital organs, which is detectable as changes in the middle cerebral artery (MCA) Doppler and the cerebroplacental ratio (CPR). The latter is a key predictor of perinatal morbidity and mortality in fetuses at risk for growth restriction
^
13,
14
^. Chronic exposure to heat with fetal blood flow redistribution could lead to reduced fetal growth
^
15,
16
^.

The detailed imaging protocol is reported elsewhere
^
7
^, but in brief the study will use trasnadominal two-dimensional ultrasound to obtain the key ultrasound parameters of the following:

At 11–14 weeks of gestation

- Crown-rump length (CRL) for pregnancy dating
^
17
^- conducted between 9 to <14 weeks and is used for all subsequent analyses, including preterm birth classification.

At each subsequent ultrasound assessment

- Biparietal diameter (BPD), head circumference (HC), abdominal circumference (AC) and femur length (FL) for biometry- Estimated fetal weight (EFW)- Amniotic fluid index easurement (AFI)- Maternal cervical length- Blood flow assessment using color flow Doppler of the Uterine artery at 18–22 and 30–34 weeks of gestation- Umbilical artery at 30–34 weeks of gestation- MCA and calculation of CPR at 30–34 weeks of gestation

In addition to the routine, detailed fetal anatomical survey performed at the second-trimester scan according to standard protocol, we will confirm that a basic structural assessment is conducted to identify any major congenital anomalies. At the same examination, placental characteristics—including location, morphology and biometric measurements—will be recorded to ensure we capture any exposure‐related vascular or placental changes.

Gestational age-based reference ranges for the pulsatility index in the umbilical artery, fetal middle cerebral artery, and the cerebroplacental ratio will be used to analyse and interpret the doppler-based placental blood flow indices. The doppler assessments will be conducted once in the third trimester (30–34 weeks of gestation) for study purposes. Repeat measurements for clinical care purposes will be as per the institutional standard of care as decided upon by the treating fetal medicine physician
^
18
^.

Fetal well-being is further assessed in the third trimester using non-invasive cardiotocography (CTG), which enables continuous monitoring of fetal heart rate (FHR) and uterine contractions, providing dynamic insights into fetal autonomic regulation and potential effects of heat-related stress. Abnormal CTG patterns—such as reduced variability, late decelerations, or tachycardia—may indicate fetal compromise and are evaluated alongside concurrent heat exposure data to explore potential associations.

Each participant undergoes CTG recording for at least 20 minutes during their third-trimester antenatal review to ensure sufficient data collection. CTGs are initially assessed in real-time during the participant’s visit using standard clinical protocols at each site. The CTG devices employed in the prospective study automatically analyse recordings using built-in computerised thresholds based on NICE and FIGO guidelines for fetal heart rate monitoring. If an abnormal result is detected, the clinician is alerted, prompting further assessment and monitoring of the mother and fetus by the hospital’s obstetrics team.

All CTG records are also transferred to a central database for further analysis using the Dawes-Redman algorithm, a validated and gold-standard method that calculates and extracts key FHR features and assesses them against the Dawes-Redman ten-point safety criteria. This automated approach minimises inter-observer variability, eliminating the need for additional inter-rater reliability checks or adjudication procedures.

All ultrasound procedures will follow a standardized imaging protocol and strict image quality control (QC) procedures drawing from previous similar protocols of INTERGROWTH & GARBH-INi using the same machine General Electric Healthcare (Illinois, USA) Voluson E8 machine
^
7
^. QC for CRL, biometry and Doppler will be conducted on 10% of images, randomly sampled, to identify any sonographers not adhering to protocol, with targeted retraining provided as needed. This QC process will be managed by an experienced team that will independently review images based on predefined criteria, ensuring high inter-rater reliability.

QC for CRL, biometry and Doppler, based on established criteria
^
19–
22
^, will be conducted on 10% of images, randomly sampled, to identify any sonographers not adhering to protocol, with targeted retraining provided as needed. This QC process will be managed by an experienced team that will independently review images based on predefined criteria, ensuring high inter-rater reliability.

### Placental circulating biomarkers

It is hypothesised that exposure to elevated environmental temperatures may impair placental function, leading to measurable alterations in circulating angiogenic and inflammatory biomarkers. A critical component of this dysfunction may involve changes in the molecular cargo of placental small extracellular vesicles (sEVs), which play a central role in mediating cell-to-cell communication during pregnancy
^
23–
25
^. Disruption of this signalling network may adversely influence maternal immune modulation, vascular function, and placental development, ultimately contributing to complications such as preterm birth, fetal growth restriction, and stillbirth. Building upon findings from the retrospective GARBH-Ini cohort (WP1a;
Figure 1), this prospective study aims to validate key placental biomarkers and elucidate mechanistic pathways implicated in heat-induced pregnancy complications. Environmental temperature exposure will be quantified using high-resolution spatiotemporal models and stratified across participants from rural and peri-urban settings in India.

Maternal venous blood samples collected at predefined gestational windows will be utilized to assess the cumulative and time-specific effects of chronic heat exposure on placental physiology. Distributed lag non-linear models (DLNM) and generalized additive models (GAM) will be used to identify critical windows of gestational vulnerability to heat exposure. Based on model-derived exposure classifications, maternal samples will be stratified into high and low exposure groups to quantify surrogate markers of placental stress. Key surrogate markers of placental stress will be quantified using immunoassay-based platforms. These include angiogenic markers (sFlt-1
^
26
^, PlGF, VEGF
^
27
^, PAPP-A
^
28
^), hormonal markers (progesterone), and inflammatory mediators (C-reactive protein [CRP], alpha-1-acid glycoprotein [AGP]
^
29,
30
^). This multi-marker approach will allow for a comprehensive assessment of placental health in the context of heat exposure. In addition, proteomic candidates previously identified in the retrospective GARBH-Ini dataset (WP1a;
Figure 1) will be evaluated in this prospective cohort to confirm differential expression in response to varying levels of heat exposure and various pregnancy outcomes. Additionally, functional validation of selected protein candidates will be conducted using
*in vitro* placental cell models to assess their role in stress-induced placental dysfunction.

The outcomes of this investigation are expected to deepen the mechanistic understanding of environmental heat stress on pregnancy and support the development of predictive biomarkers for early diagnosis and intervention in heat-related adverse pregnancy outcomes.

### Lactation assessment

Extreme heat exposure around birth is postulated to delay lactation onset after childbirth, reduce milk volume, and alter lactation hormones such as prolactin
^
31,
32
^. This sub-objective will be investigated in a targeted subset of 100 women in the lactation study (50 from the winter cohort and 50 from the summer cohort) all recruited from the GCH site. Four characteristics of lactation will be measured: (i) Timing of lactation onset assessed daily using a validated breast fullness scale during postpartum days 1–4, with a score of 3 or more indicating lactation onset
^
32
^; (ii) Milk maturation will be monitored daily/alternate days basis from days 1–16 by measurement of milk Na
^+^ and K
^+^ using portable ion electrodes (Horiba Na
^+^ and K+ laqua twin probes, Kyoto, Japan); (iii) The composition of colostrum, transitional milk, and mature milk will be characterised using a mid-infrared spectroscopy-based human milk analyzer, with foremilk and hindmilk nutrients being specifically assessed, and samples stored at -80°C for further analysis; (iv) Serum lactation hormones, particularly prolactin, will be measured before and after breastfeeding on postpartum days 15–16
^
33
^. During the lactation assessment, at least one measurement of heat stress and PM 2.5 in the home will be captured.

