### Inclusion criteria

Pregnant women fulfilling the following inclusion criteria will be considered eligible if they have:

Confirmed singleton pregnancyGestational age between 11 and 13+6 weeks at the time of recruitment, determined by ultrasound-based crown-rump length measurementRecruitment during predefined seasonal windows corresponding to site-specific climatic extremes:Gurugram: warm season (April–July) and cool season (November–February)Puducherry: warm season (March–June) and cool season (November–February)Chhattisgarh: warm season (March–June) and cool season (November–February);Elevated risk of heat exposure based on occupational or household factors, including employment in agriculture, construction, factories, or street vending; residence in poorly ventilated homes, homes with metal roofing, or use of traditional biomass stoves (chulhas)Willingness and ability to provide informed consent and participate in all study assessments, including home- and workplace-based environmental monitoring throughout pregnancy

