### Sample size

This exploratory study will be powered primarily on multiple physiological and biochemical outcomes, rather than on clinical endpoints, many of which currently lack sufficient preliminary data to enable formal power calculations at the 5% significance level.

Primary outcomes:

Physiological and biochemical measures include maternal core body temperature, urine specific gravity, maternal cardiac output (USCOM), heart rate variability, and angiogenic ratio (sFlt-1/PlGF). Clinical outcomes include preterm birth (<37 weeks of gestation) and birth weight (grams).

Secondary outcomes:

Secondary endpoints comprise gestational age (weeks), small for gestational age (SGA), stillbirth, and additional placental and fetal biomarkers.

A total of 700 pregnant women will be enrolled to account for an anticipated attrition rate of approximately 15%, yielding an expected final sample of about 600 mother–baby dyads with complete follow-up. The majority of outcomes are continuous variables, which—following transformation to approximate normality, if required—will provide 80% statistical power at a two-sided significance level of α = 0.05 to detect a minimum difference of 0.23 standard deviations between high versus low heat exposure groups. This detectable effect size lies well within accepted thresholds for clinical relevance.

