## Structured summary

Public title: Heat in Pregnancy – IndiaScientific title: Effects of extreme heat on maternal, placental and fetal physiology, lactation and newborn health in IndiaStudy design: Prospective cohort studyStudy population: Pregnant women enrolled in the first trimester in three sites: Gurugram, Chhattisgarh, PondicherrySetting: Mixed hospital and community-based recruitment sites in Gurugram, Chhattisgarh, Pondicherry during winter and summer monthsTarget sample size: 600 participants (300 in the summer group and 300 in the winter group)Intervention/exposure: Natural seasonal heat exposure (participants recruited in summer vs. winter months)Comparator/control: Women recruited in winter months serve as the comparator groupPrimary outcomes: Incidence of preterm birth (<37 weeks); birth weightSecondary outcomes: Gestational age, stillbirth, and other maternal/newborn health outcomesKey inclusion criteria: Pregnant women in 11–14 weeks, aged 18–45 years, residing in the area for at least 6 monthsKey exclusion criteria: Women with pre-existing chronic illnesses or those unlikely to remain in the area during follow-upStudy period: Expected recruitment from May 2023 to March 2026

Ethics approval: Approved by

1.Translational Health Science and Technology, Institute, Faridabad (THS 1.8.1/ (171)2.Gurugram Civil Hospital (GCH/EC/2021/1826/8.12.2023/28.1)3.Chhattisgarh Institute of Medical Sciences, Bilaspur (327/C.I.M.S/I.E.C/2024)4.Pondicherry Institute of Medical Sciences, Puducherry (RC/2024/08)5.The George Institute for Global Health, India (Project Number 31/2023)6.Sri Ramachandra Institute of Higher Education and Research (IEC/24/MAR/185/07)•Trial registration: Clinical Trials Registry of India (CTRI)-(CTRI/2024/12/078527), registered on 24/12/2024 open for 3 years.•Data sharing: De-identified participant data and metadata will be shared through Zenodo, a public repository:
**
10.5281/zenodo.16421773
**
•Funding source: Supported by the Wellcome Trust

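### The lactation subset is split by season of recruitment, yet its hypothesis concerns heat around birth, when Gurugram's winter recruits are the hot-season group and its summer recruits the cool-season group

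*Protocol article*

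**What the plan says.** The Lactation assessment section gives the hypothesis as "Extreme heat exposure around birth is postulated to delay lactation onset after childbirth". It takes measurements in the first days and weeks after delivery: onset on days 1–4, serum prolactin on days 15–16, and "Milk maturation will be monitored daily/alternate days basis from days 1–16". The 100 women are "50 from the winter cohort and 50 from the summer cohort) all recruited from the GCH site". The section does not define the two cohorts.

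The definition has to come from elsewhere in the article. Inclusion criteria fixes recruitment at 11 to 13+6 weeks within seasonal windows: "Gurugram: warm season (April–July) and cool season (November–February"). The Structured summary gives the exposure as "Natural seasonal heat exposure (participants recruited in summer vs. winter months") and makes the winter recruits the comparator. No section defines a cohort by season of birth or mentions the half-year between recruitment and delivery.

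On exposure data, the Lactation assessment section adds: "During the lactation assessment, at least one measurement of heat stress and PM 2.5 in the home will be captured". Table 1 lists heat and indoor pollution measurement at the postnatal visit. Statistical approach includes early lactation among the outcomes to be related to environmental exposures. It also places season or recruitment timing in the adjustment set and plans analyses stratified by recruitment season.

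**The concern.** The cohort label describes the season at about three months of gestation. The lactation hypothesis is about the season some six months later. At a site with one warm and one cool recruitment window, a shift of that length turns one season into the other.

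Two things are at stake. First, if the 50 and 50 are compared under their labels, with winter as the low-heat comparator, a harmful effect of heat on lactation onset, milk maturation or prolactin would appear as a benefit. Second, at a single site recruitment season nearly determines birth season. Carrying the general adjustment or stratification by recruitment season into this subset would therefore take out the contrast that the 50/50 split creates.

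**Working it through.** **The plan's own figure.** Sample size gives a detectable difference of 0.23 SD at "80% statistical power at a two-sided significance level of α = 0.05". With 300 per group, 2.802 × √(2/300) = 0.229 SD, so the figure reproduces. It is for the whole cohort. The article gives none for the lactation subset. The same formula with 50 per group gives 2.802 × √(2/50) = 0.560 SD.

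**Inputs for the dates.** Gurugram windows are April–July and November–February (Inclusion criteria). Gestation at entry is 11+0 to 13+6 weeks, that is 77 to 97 days (same section). Gestation at birth is an assumption, taken first as 40 weeks (280 days).

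**Formula.** Birth date = recruitment date + (gestation at birth − gestation at entry). At 40 weeks the interval runs from 280 − 97 = 183 to 280 − 77 = 203 days.

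- Winter recruits: 1 November + 183 days = 3 May; 28 February + 203 days = 19 September.
- Summer recruits: 1 April + 183 days = 1 October; 31 July + 203 days = 19 February.

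**Range of term births.** The lower limit of 37 weeks comes from the article's definition of "preterm birth (<37 weeks of gestation"). The upper limit of 42 weeks is assumed. Winter recruits then deliver between 12 April and 3 October, and summer recruits between 10 September and 5 March. The two spans meet only at their extremes.

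**Share of births in the site's own windows.** Simulated with recruitment uniform over each window and entry gestation uniform over 77–97 days (both assumptions):

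| Gestation at birth (weeks) | Winter recruits, April–July | Winter recruits, Nov–Feb | Summer recruits, April–July | Summer recruits, Nov–Feb |
|---|---|---|---|---|
| 40, fixed | 66.7% | 0% | 0% | 82.8% |
| 39, fixed | 72.6% | 0% | 0% | 76.9% |
| 39, SD 1.7 | 72.5% | 0% | 0% | 76.9% |
| 38.5, SD 2 | 75.3% | 0% | 0% | 73.9% |

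The reversal holds in every row. The remaining births fall mainly in August–September for winter recruits (25–33%) and mainly in October for summer recruits (17–26% outside November–February).

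**Recruitment season as a covariate.** Conditioning on it removes the difference between the two cohorts. What is left is the variation within each cohort's span of births: at 40 weeks, 139 days (3 May–19 September) and 141 days (1 October–19 February).

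**The case against.** The strongest reply is that the Lactation assessment section uses the split only to say where the 100 women come from. It does not name the cohort label as the exposure. Heat is to be measured in the home during the lactation assessment, Table 1 repeats this, and satellite temperature and humidity are retrieved for the whole pregnancy (Individual environmental exposures). Statistical approach speaks of associations with environmental exposures, and the details belong to the analysis plan. The Structured summary, which does name winter recruits as comparator, lists preterm birth and birth weight as its primary outcomes and does not mention lactation.

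Much of this stands. A reader might infer that the lactation results will come out with the wrong sign. The article does not support that: the wrong sign follows only if the cohort label is the exposure, and a model on measured heat is free of it. A reader might also infer that the design has lost its seasonal contrast. It has not, because the two cohorts are almost fully separated by season of birth.

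A third tempting inference is a loss of power, found by dividing 0.56 SD by the 0.67–0.75 of winter recruits' births that fall in April–July, which gives about 0.74–0.84 SD. That would treat August–September births as no hotter than November–February births. The article gives no monthly temperatures, and April–July is a recruitment window, not a statement that August is cool. The loss cannot be quantified.

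What the reply does not remove is the grouping itself. The only group structure stated for this sub-study runs opposite to its hypothesis, the only stated comparator is the hot-season group at birth, and the general plan conditions on recruitment season without an exception for lactation.

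**Conclusion.** For a hypothesis about heat around birth, the summer and winter labels and the winter comparator are reversed. The labels are correct for recruitment, and the reversal concerns the perinatal period only. Any lactation contrast by label would have the wrong sign, and conditioning on recruitment season would remove most of the perinatal heat contrast. A model on measured heat without that conditioning would not have the sign problem.

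The dates rest on the article's own windows and entry gestation plus an assumed gestation at birth, and the reversal survives every value tried. The shares (about 67–75% and 74–83%) also assume uniform recruitment and use the site's recruitment windows as its hot and cool seasons. Reading the cohorts as recruitment groups rests on Inclusion criteria and the Structured summary, and nothing in the article supports another reading.

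Severity is moderate. The sub-study has 100 women, the study calls itself exploratory, and no lactation measure is among the listed primary or secondary outcomes.

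**What to change.** - Fill the two sets of 50 by expected delivery date, hot-season against cool-season births, as far as Gurugram enrolment allows, and name them by season of birth.
- State that heat measured in the home or derived from satellite data around birth (days 0–16 postpartum) is the lactation exposure.
- State that, for this sub-study, recruitment season is not the exposure, the comparator, an adjustment variable or a stratification variable.
- Reconcile the Structured summary so that winter recruits are not read as the low-heat comparator for lactation.

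The cost is small. The dating scan already gives the expected delivery date, and the site, the number of women and the lactation measurements do not change. Satellite retrieval, now described for the pregnancy, would run about two weeks longer.

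If births are restricted to the site's own windows, 50 in April–July need about 67 to 75 winter recruits (50/0.753 to 50/0.667). Fifty in November–February need about 61 to 68 summer recruits (50/0.828 to 50/0.739), in both cases before losses. The article gives no enrolment target per site, so the team has to confirm that these numbers are available. The rule should change before the 100 women are chosen, because later analysis cannot alter when they gave birth.
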